### Assessments

2.3

Participants complete a baseline interview prior to treatment randomization to establish diagnoses and symptom presentation in addition to interviews at the end-of-treatment (approximately 6 weeks post-randomization) and 1-, 3-, and 6-months post-treatment. Brief self-report assessments are administered 2-3 times per week throughout the treatment course. Participants are compensated for interviews but not for treatment sessions. All assessments are administered by experienced, blinded examiners at the Master's or doctoral-level with a minimum inter-rater reliability of .80 on PTSD and SUD clinical interviews. To determine inter-rater reliability over the study course, 10% of interviews will be randomly selected to be independently scored by licensed, Ph.D.-level researchers. Assessments include a combination of diagnostic interviews and self-report measures. The primary outcomes of interest are changes in PTSD symptoms, substance use frequency and problems, depressive symptoms, and quality of life. Additional focal assessments include measures of trauma-related cognitions and substance use craving. See Table 1 for the assessment schedule.

**Table 1 tbl1:** Patient assessment schedule.

Measure	Purpose	Format	Pretreatment	During Treatment	At End of Treatment	1-, 3-, 6 Month Post-treatment
P-4 Suicide Severity Rating Scale	Eligibility, secondary outcome	Interview	X	-	X	X
Structured Clinical Interview for DSM-5	Characterize Sample	Interview	X	-	-	-
Clinician Administered PTSD Scale-5	Eligibility, Primary Outcome	Interview	X	-	X	X
Timeline Follow Back Interview	Primary Outcome	Interview	X	-	X	X
PTSD Checklist –DSM-5	Secondary Outcome, Mediator, Within Treatment Change	Self-Report	X	X	X	X
Short Inventory of Problems Revised (SIP-R)	Primary Outcome	Self-Report	X		X	X
Substance Use Inventory (SUI)	Secondary Outcome, Within Treatment Change	Self-Report	X	X		
Patient Health Questionnaire-9	Secondary Outcome	Self-Report	X	-	X	X
Brief Inventory of Psychosocial Functioning	Secondary Outcome	Self-Report	X	-	X	X
WHO – Disability Assessment Schedule	Secondary Outcome	Self-Report	X	-	X	X
Brief Substance Craving Scale	Secondary Outcome, Within Treatment Change	Self-Report	X	X	X	X
Posttraumatic Cognitions Inventory	Mediator		X	X	X	X
Treatment Services Review	Characterize Sample, Potential Covariate	Interview	-	-	X	X
Demographic Questionnaire	Characterize Sample, Moderator	Self-Report	X	-	-	-

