#### Treatment outcomes analyses

2.8.2

Primary outcomes comprise the CAPS-5 PTSD severity and TLFB percent days of substance use. PTSD-related cognitions and substance use craving will be examined as potential outcome mediators of intervention effects on the primary outcomes, the remaining follow-up measures discussed above comprise secondary outcomes. Generalized linear mixed models (GLMMs) will be used to model treatment outcomes with the form of GLMM chosen to well-model the respective outcome. The models will include fixed effects for follow-up time, treatment condition, and their interaction together with random intercepts for participants. We expect outcomes to vary by gender, age, race/ethnicity, and baseline PTSD severity so the models will include these as additional fixed effects. Missing data will be addressed using multiple imputation by chained regressions within intervention arms. Wald tests will assess whether there is an interaction between treatment condition and time of follow-up using results aggregated over models fit to the imputed datasets; if there is no such interaction, a Wald test will assess whether there is a main effect for treatment condition.

Secondary exploratory analyses will assess gender as a potential moderator of treatment effects as work has suggested women may show greater treatment gains in trauma-focused therapies compared to men and women have higher rates of developing PTSD prior to an SUD compared to men [27,60]. The potential mediating roles of changes in PTSD-related cognitions and substance use craving on treatment outcomes will be investigated and we will investigate whether changes in PTSD symptomology mediate subsequent changes in substance use outcomes. We will implement multiple analyses to investigate these potential mediation pathways. For each follow-up, we will fit generalized linear models (GLM) for the mediators and outcomes to implement the potential outcomes causal mediation analyses described by Imai et al. [61] These analyses will generate estimates of average direct and average causal mediation effects of the intervention on the outcomes. Alternate longitudinal causal mediation analyses, particularly those examining time-lagged effects of changes in PTSD symptomatology on subsequent SUD outcomes, will develop and employ marginal structural models.

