Sample size was determined using Monte Carlo simulation considering uniform 30% dropout over time, correlations between outcomes across time of .30, a group standardized effect for PTSD symptoms and days substance use of .58 (Cohen's d) based on our previous research, and a .05 significance level. A sample size of 168 subjects provides >80% power to identify between group effects under these conditions.

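### The random-intercept model leaves the treatment-by-time test and late-versus-early contrasts exposed if CAPS-5 correlation decays over follow-up; a freer covariance is a cheap safeguard

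*Protocol article*

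**What the plan says.** Section 2.8.2 names two primary outcomes: "Primary outcomes comprise the CAPS-5 PTSD severity and TLFB percent days of substance use". The distributional form is left open by outcome: "Generalized linear mixed models (GLMMs) will be used to model treatment outcomes with the form of GLMM chosen to well-model the respective outcome". The next sentence sets the fixed and random effects for all the models: "The models will include fixed effects for follow-up time, treatment condition, and their interaction together with random intercepts for participants".

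The tests run in sequence. A Wald test of treatment by time comes first; then, "if there is no such interaction, a Wald test will assess whether there is a main effect for treatment condition". On missing data: "Missing data will be addressed using multiple imputation by chained regressions within intervention arms".

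Section 2.3 puts the post-baseline interviews at "end-of-treatment (approximately 6 weeks post-randomization) and 1-, 3-, and 6-months post-treatment". The gaps between successive follow-ups are therefore about 1, 2 and 3 months. The only statement about dependence over time is the sample-size input in section 2.8.2, "correlations between outcomes across time of .30". The article does not say whether time enters as categories or as a linear term, and it announces no visit-specific intervals.

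**The concern.** For a Gaussian outcome, a participant-level random intercept with independent residuals implies the same variance at every visit and the same correlation for every pair of visits. Repeated symptom scores often correlate less as the gap widens, and here the gaps range from 1 month to 6 months. If that happens, the model overstates the correlation between distant visits and understates the variance of changes between them. The treatment-by-time test is built from such changes, and it decides whether the main effect is tested at all. Any late-versus-early contrast used to explain an interaction has the same weakness.

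Changing variance is a separate mechanism. If the SD grows over follow-up, the pooled variance is too small at 6 months and too large at end of treatment.

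**Working it through.** **Inputs from the article.** 168 participants, equal allocation (84 per arm); visits at 0, 1, 3 and 6 months after treatment; effect .58 SD; correlation .30; 30% dropout; alpha .05, taken as two-sided.

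**Assumptions.** The decay rates and SD patterns below are assumed, because the article gives none.

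**Step 1: the plan's own power figure.** At one visit with 84 × .7 = 58.8 per arm, SE = √(2/58.8) = .184. Power = Φ(.58/.184 − 1.96) = 88.2%. Without dropout it is 96.4%. For the mean of four visits the variance factor is (1 + 3 × .30)/4 = .475, which gives 99.5% even at 58.8 per arm. All agree with the stated figure of more than 80%.

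**Step 2: what the model assumes against what may be true.** With balanced data, the random-intercept model estimates the mean of the four variances and the mean of the six covariances. Call that matrix C and the true one S. For a contrast w, type I error = 2[1 − Φ(1.96 √(w′Cw / w′Sw))]. For the 3-df interaction with contrast matrix L, it is P(Σ λᵢχ²₁ > 7.815), where λᵢ are the eigenvalues of (LCL′)⁻¹(LSL′).

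Worked example, decay .8 per month with equal SDs:
- The six correlations are .80, .51, .26, .64, .33 and .51, with mean .509.
- 6 months minus end of treatment: true variance 2(1 − .262) = 1.476, model variance 2(1 − .509) = .982. Error = 2[1 − Φ(1.96 √(.982/1.476))] = 11.0%.
- Linear slope: centred times −2.5, −1.5, .5, 3.5, sum of squares 21. Model variance (1 − .509)/21 = .0234, true variance .0420. Error = 14.4%.

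Complete data, equal SDs:

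| Correlation pattern | Mean correlation | 3-df interaction | 6 months vs end of treatment | Linear interaction |
|---|---|---|---|---|
| constant .30 | .30 | 5.0% | 5.0% | 5.0% |
| decay .65 per month | .30 | 6.0% | 8.9% | 11.8% |
| decay .7 per month | .36 | 6.1% | 9.5% | 12.6% |
| decay .8 per month | .51 | 6.5% | 11.0% | 14.4% |
| decay .9 per month | .71 | 7.0% | 12.6% | 16.2% |

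The visit-averaged main effect is 5.0% in every row.

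**Step 3: milder decay.** Visit-level noise can be added so that correlations decay but average .25 to .29 (decay .8 applied to 50% of the variance, or .9 to 40%). The 3-df test is then 5.1–5.2%, the late-versus-early contrast 6.2–6.9%, and the linear test 6.8–8.1%.

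**Step 4: with the planned imputation.** Simulation used 84 per arm, dropout of 0/10/20/30% completely at random, 20 imputations within arm, and 1,000–1,500 trials per case. With decay of .7 to .9, the 3-df test has about 4–6% error, the late-versus-early contrast 8–11%, and the linear interaction 10–13%. Between-imputation variance offsets part of the error. Replacing the model covariance by the empirical one returns all three to about 4–6%.

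**Step 5: available data without imputation.** Under the same dropout and 2,000 trials per case, a likelihood fit gave 7.1–9.0% (categorical) and 11.8–17.8% (linear) under decay, with or without a rising SD. Cluster-robust errors gave 4.6–6.3% in all cases.

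**Step 6: rising variance.** For SDs of 1, 1.1, 1.2 and 1.3, the mean variance is 5.34/4 = 1.335. The arm difference at 6 months has error 2[1 − Φ(1.96 √(1.335/1.69))] = 8.2%; at end of treatment, 2[1 − Φ(1.96 √1.335)] = 2.4%. With the SD rising to 1.4 and dropout, simulated 95% coverage was 88–91% at 6 months and 97–98% at end of treatment. With equal SDs it was 93.5–96% even under decay.

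**The case against.** A reader might infer that the interaction test and the visit-specific error bars are simply wrong. The document does not support that, for five reasons.

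- The harm is conditional. Under a constant correlation of .30 and equal variances, the model is correctly specified and the test has nominal size. Unequal spacing alone is not a fault. Still, the .30 is a planning input, not evidence of constancy, and a decaying pattern with the same mean already gives 11.8% for a linear interaction.
- With categorical time and the planned imputation, the gating test is about nominal. This stands; the larger errors belong to linear time and to the follow-up contrasts.
- The plan announces no visit-specific intervals or 6-month contrast. This also stands, although a significant interaction can hardly be interpreted without such contrasts.
- Equal variance and correlation are not forced on percent days of use if it is modelled with a non-Gaussian form. The plainest reason for expecting changing variance concerns that outcome: residential stays of roughly 30 to 90 days (section 2.2.1), and recall windows that differ in length (section 2.3.1). The Gaussian figures should not be carried over to it.
- Robust errors or a residual structure would be compatible with the text and may be in the unseen analysis plan. Their absence from an article is not an error. The point rests on the random-effects structure that the article does state.

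**Conclusion.** The point holds as a conditional weakness. If CAPS-5 correlation decays at about .7 to .9 per month, a linear treatment-by-time test has about 13–16% error on complete data and 10–13% after imputation. A categorical test has about 4–7%, and the 6-month versus end-of-treatment contrast about 7–13%. Under the mildest pattern tried, the linear test falls to 6.8% and the contrast to 6.2%. Rising variance would separately narrow 6-month intervals and widen end-of-treatment ones.

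The visit-averaged main effect is 5.0% on complete data and 4.2–5.7% in simulation, apart from 7.4% in the most extreme case. Power for a constant .58 effect stayed at 95% or more, so 168 participants remains adequate. All error rates rest on assumed decay and SD patterns. This is a cheap improvement, not a defect that invalidates the primary analysis.

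**What to change.** For CAPS-5, state that time is categorical and replace the random intercept with an unstructured covariance over the four follow-ups. For percent days of use and other non-Gaussian outcomes, keep the random intercept but base the Wald tests on participant-clustered robust standard errors. Pool over imputations as planned.

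The cost is a sentence or two of analysis wording, with no new data and no change in sample size. The unstructured matrix has 4 variances and 6 covariances, so 10 parameters instead of 2, which 168 participants can support. If the simpler structure was in fact true, intervals will be slightly wider. The trial is ongoing, so the change can be made before analysis.

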### Treatment

2.2

Eligible participants are randomly assigned to TAU or M-PE with randomization stratified by residential or outpatient treatment using randomly permuted-blocks with equivalent allocation to each treatment group. Randomization will be computer-generated with all clinical assessors blinded to treatment condition. Individual conditions are described below. For both TAU and M-PE, potential substance use during treatment is managed on a case-by-case basis by treatment site staff and decisions are made independently of this study.

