#### Treatment as usual (TAU)

2.2.1

The treatment site offers comprehensive care including detoxification, residential and outpatient programs, and recovery housing. Typical length of stay in residential care is approximately 30 to 90 days tailored to individual need. Patients in the residential program engage in care from 7:30am to 5:00pm Monday through Friday with optional programming on weekends and evenings. Typical length of comprehensive outpatient participation is person-centered with length of participation contingent upon individual need. Individuals in the outpatient program participate in group and individual therapy up to 3 days per week depending on need. Providers at the treatment site come from multidisciplinary backgrounds including licensed social workers, Master's and doctoral level clinicians, licensed marriage and family counselors, and nurse practitioners.

**SUD TAU.** Services are tailored to the patient and include individual and group therapy, 12 steps groups, family counseling, medication management, and social support services that implement a variety of evidence-based approaches such as motivational interviewing and cognitive behavioral therapy.

**Trauma TAU.** Participants engage in a resiliency, skills-based group based on adaptations of the Seeking Safety curriculum and comprised of five 90-min standalone sessions. These sessions focus on development of coping skills and symptom management without exposure to the traumatic event.

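### Randomisation is stratified by residential versus outpatient setting, but the listed outcome-model terms omit setting, so the main-effect test is conservative if setting is prognostic

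*Protocol article*

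**What the plan says.** Section 2.2 of the protocol article specifies "randomization stratified by residential or outpatient treatment using randomly permuted-blocks with equivalent allocation to each treatment group".

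Section 2.8.2 sets out the outcome models. The core is "The models will include fixed effects for follow-up time, treatment condition, and their interaction together with random intercepts for participants". The adjustment set follows: "We expect outcomes to vary by gender, age, race/ethnicity, and baseline PTSD severity so the models will include these as additional fixed effects". Setting is in neither sentence, and no other section adds it.

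The same section names the primary outcomes ("Primary outcomes comprise the CAPS-5 PTSD severity and TLFB percent days of substance use") and a two-step test. Treatment-by-time is tested first, and "if there is no such interaction, a Wald test will assess whether there is a main effect for treatment condition".

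Two other places bear on whether setting matters. Section 2.2.1 states: "Typical length of stay in residential care is approximately 30 to 90 days tailored to individual need". Section 2.3.1 says that TLFB interviews after baseline cover every day since the previous assessment, and that participants mark days in a controlled environment, with residential care among the examples.

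**The concern.** Stratified permuted blocks make the arms alike on setting, so between-setting variance drops out of the true sampling variance of the treatment contrast. A model without setting still counts that variance as noise. Its standard error then overstates the real uncertainty, and the test rejects less often than its nominal level.

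The investigators thought setting important enough to stratify on, yet left it off the list of variables expected to drive outcomes. Because the article names its adjustment set and gives a reason for it, this is a stated choice and not a detail left to the analysis plan.

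Setting is plausibly prognostic for substance use. If a resident is randomised at admission (an assumption), a stay of 30 to 90 days covers 30/42 = 71% to 100% of the roughly 6-week end-of-treatment window. Those are controlled-environment days. Nothing in the article links setting to CAPS-5 in the same way, and baseline PTSD severity is already in that model.

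At stake are a correctly calibrated main-effect test and some precision.

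**Working it through.** **Inputs from the article.** N = 168, allocated equally; d = 0.58; significance level 0.05 (two-sided assumed); "uniform 30% dropout over time, correlations between outcomes across time of .30"; four follow-up visits (end of treatment, then 1, 3 and 6 months).

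**Input not in the article.** The share of single-visit outcome variance due to setting, R². Assumed 0.05 to 0.10, with 0 and 0.20 as bounds for comparison.

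**1. The plan's own power figure.** Completers per arm: 168 × 0.7 / 2 = 58.8. At a single visit, z = 0.58 / √(2/58.8) = 3.145, and power = Φ(3.145 − 1.96) = 88.2%. The stated figure of more than 80% is reproduced. The minimum for 80% is 47 per arm, so 94 / 0.7 gives 135 after dropout, fewer than 168.

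**2. Setting effect constant over four visits.** The variance of the four-visit mean at correlation 0.30 is (1 + 3 × 0.30)/4 = 0.475. The share due to setting is R²/0.475. The actual level is 2[1 − Φ(1.96/√(1 − share))], and the patient equivalent is 1/(1 − share).

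**3. Setting effect in only k of the four windows.** The share becomes (k/4)² × R²/0.475.

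| Windows affected | R² | Share | Actual level of a nominal 5% test | Patient equivalent |
|---|---|---|---|---|
| 4 | 0.05 | 0.105 | 3.8% | 1.12 |
| 4 | 0.10 | 0.211 | 2.7% | 1.27 |
| 2 | 0.05 | 0.026 | 4.7% | 1.03 |
| 2 | 0.10 | 0.053 | 4.4% | 1.06 |
| 1 | 0.05 | 0.007 | 4.9% | 1.01 |
| 1 | 0.10 | 0.013 | 4.85% | 1.01 |

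The patient equivalent compares the variances that the two models report. Stratification has already given the estimator most of the precision, and the model without setting fails to credit it. These formulas ignore dropout and the other covariates.

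**4. Simulation of the constant-effect case.** Random-intercept model, identity link, four visits, 30% monotone dropout, blocks of 4 in two equal strata, 4,000 null trials per row:

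| R² | Model SE without setting | Empirical SE | Type I error without setting | Type I error with setting |
|---|---|---|---|---|
| 0 | 0.115 | 0.113 | 0.048 | 0.052 |
| 0.05 | 0.115 | 0.110 | 0.040 | 0.051 |
| 0.10 | 0.115 | 0.103 | 0.030 | 0.053 |
| 0.20 | 0.115 | 0.092 | 0.014 | 0.058 |

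This agrees with step 2.

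**5. Effect on power.** At a single visit with 58.8 per arm, omitting setting gives Φ((3.145 − 1.96)/√(1 − R²)) = 88.8% at R² = 0.05 and 89.4% at 0.10. Including it gives Φ(3.145/√(1 − R²) − 1.96) = 89.7% and 91.2%. The gain is about 1 to 2 points, and both stay above 80%.

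**The case against.** The strongest reply is that this is a small matter of efficiency. The test errs on the safe side, the stated power survives, and every figure for the loss rests on an assumed R². All of that stands and limits the weight of the point.

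A reader might infer four stronger things, none of which the article supports:

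- **That setting is the largest source of variation in substance-use days.** No section gives a use rate, standard deviation or variance by setting, or ranks the sources. Controlled-environment days also include detoxification, hospitalisation and incarceration, so they are not confined to residents.
- **That the omission shrinks the treatment coefficient in a non-linear GLMM.** This is not shown for a model with participant random intercepts, which largely absorb a person-level factor. In a simulated random-intercept logistic model (true coefficient −0.60, random-intercept SD 1.5), the estimate was −0.600 without setting and −0.601 with it for a setting effect of 1.0 logit. At 2.0 logits it was −0.616 and −0.613.
- **That 12-27% is the expected loss.** It requires a setting effect undiminished through 6 months. The argument from residential days points to the early windows, where the figure is 1-6%.
- **That every test is affected.** The treatment-by-time test, which comes first, rests mainly on within-person contrasts and is little changed by a constant setting effect. A setting effect that changes over follow-up would matter there.

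It can also be said that the article does not list the imputation variables and does not exclude further covariates. The first is fair: the imputation step here is a recommendation, not a fault found. The second is weaker, because the article gives a reasoned list and the stratification factor is not on it.

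**Conclusion.** The point holds as a modest one. The article stratifies by setting and then lists model terms that omit it. If setting is prognostic, the treatment main-effect test is conservative and loses some efficiency, more plausibly for TLFB percent days than for CAPS-5.

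The size cannot be fixed from the article. At an assumed 5-10% of single-visit variance, the nominal 5% test runs somewhere between about 4.9% and 2.7%, depending on how long the setting effect lasts. At R² = 0 the omission costs nothing. These sizes are for an identity link. The article does not state the GLMM form for percent days, and sizes on another scale may differ.

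**What to change.** Add setting at randomisation (residential or outpatient) to the fixed effects in section 2.8.2 for every outcome GLMM, and state that it is also in the imputation model. The Discussion expects attendance and continuation difficulties as participants move from residential to outpatient care, so missingness may depend on setting.

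A setting-by-time interaction for TLFB percent days is optional. It would take three further terms with four visits, and would address a setting effect that fades as residents leave care.

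The cost is a change of wording and one model term, using a variable already recorded at randomisation. The trial is ongoing, so making the change now keeps the covariate prespecified.

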#### Assessor administered measures: baseline and follow-up interviews

2.3.1

**PTSD Diagnostic Interview**. The clinician-administered PTSD Scale for DSM 5 (CAPS-5) [36] is the primary PTSD symptom measure. At baseline, the CAPS-5 is used to determine presence of PTSD and pre-treatment PTSD severity. Items are rated on both frequency and intensity to derive a severity score for each symptom ranging from 0 (absent) to 4 (extreme). Items scored at a severity of 2 (moderate) or higher are considered “present” and counted toward the total number of symptoms required for each DSM-5 symptom cluster. DSM-5 requires presence of 1 or more re-experiencing symptoms (cluster B), 1 or more avoidance symptoms (cluster C), 2 or more alterations in cognition or mood symptoms (cluster D), and 2 or more arousal symptoms (cluster E). The present study allows individuals to be subthreshold by 1 symptom. The CAPS-5 also assesses dissociation symptoms, social and occupational functioning, and response validity.

**Substance Use Interviews**. The Structured Clinical Interview for DSM-5 (SCID) [37] is used to assess for presence of SUD(s) at baseline. The Timeline-Follow back (TLFB) [38] is used to assess frequency of substance use and percent of substance use days. At baseline, the TLFB assesses the 90 days prior to baseline. Subsequent interviews assess the period between the last assessment and the current interview date to allow for coverage of all days of the study period. During the TLFB, participants note any dates in which they were in a controlled environment (e.g., residential care, detoxification, hospitalization, incarceration).

**Additional Interview Measures**. Suicidal ideation is assessed using the P4 [39]. This interview assesses current suicidal ideation, plans, and intent as well as history of suicidal thoughts and behaviors. The Treatment Services Review (TSR) [40] assesses participation in various interventions (e.g., individual therapy, residential treatment, detoxification, psychopharmacological intervention) as a total count of times each service was received since the last interview.

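### The listed covariates give the CAPS-5 model its own baseline but not the TLFB model or the non-PTSD secondary models, at a cost in precision, not validity

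*Protocol article*

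**What the plan says.** Section 2.8.2 (Treatment outcomes analyses) names two primary outcomes: "Primary outcomes comprise the CAPS-5 PTSD severity and TLFB percent days of substance use". One model form serves all outcomes: "The models will include fixed effects for follow-up time, treatment condition, and their interaction together with random intercepts for participants". The covariates follow in one sentence, which names gender, age, race/ethnicity and "baseline PTSD severity so the models will include these as additional fixed effects". Baseline substance use is not among them, and no rule says that each outcome is adjusted for its own baseline value.

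Section 2.3.1 shows that both primary outcomes have a baseline measurement. For PTSD: "At baseline, the CAPS-5 is used to determine presence of PTSD and pre-treatment PTSD severity". For substance use: "At baseline, the TLFB assesses the 90 days prior to baseline". Table 1 also marks SIP-R, PHQ-9, BIPF, WHODAS and the craving scale as collected before treatment. (Table 1 labels SIP-R primary; section 2.8.2 makes it secondary. That does not affect this point.)

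The follow-up assessments are "interviews at the end-of-treatment (approximately 6 weeks post-randomization) and 1-, 3-, and 6-months post-treatment", so there are four. On missing data, the article says: "Missing data will be addressed using multiple imputation by chained regressions within intervention arms". It does not list the predictors in the imputation.

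**The concern.** In a randomised trial with a continuous or near-continuous outcome, the outcome's own pre-treatment value is usually its best single predictor. Adjusting for it removes between-person variation that would otherwise sit in the standard error of the treatment effect. The plan does this for CAPS-5, because baseline PTSD severity is measured by CAPS-5. It then carries the same covariate over to the substance-use outcome, where PTSD severity is at best an indirect stand-in for earlier use.

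At stake is the precision of a primary comparison. Randomisation is stratified by residential or outpatient setting only (section 2.2), so the design does not balance baseline use either. The data that would recover the precision are already collected.

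**Working it through.** **Inputs.** From the sample-size paragraph of section 2.8.2: N = 168, standardised effect .58 for PTSD symptoms and for days of use, correlation across time ρ = .30, 30% dropout, significance level .05 (taken as two-sided). From section 2.2: equal allocation, so 84 per arm. From section 2.3: four follow-up assessments.

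**Assumptions.** The correlation r between baseline and follow-up TLFB is not given, so I take r = .30 by extending ρ and show .10 and .50. It should be read as the correlation left after the covariates already listed. The scale is linear. Dropout is monotone and evenly spread, so 92.5%, 85%, 77.5% and 70% are seen at visits 1 to 4. Thus 7.5% have exactly one visit, 7.5% two, 7.5% three and 70% four.

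**The plan's own figure.** At one visit with 84 × .70 = 58.8 per arm:
.58 × √(58.8/2) − 1.96 = 3.145 − 1.96 = 1.185, so power is 88.2%. The stated figure above 80% is reproduced with no TLFB baseline in the model.

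**Complete data, average of four visits.**
- Variance without own baseline: (1 + 3ρ)/4 = 1.9/4 = .475.
- Reduction from own baseline: r² = .09.
- Proportion: .09/.475 = 18.9%.

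**With dropout.** A person with j visits contributes information 1/[(1 + (j − 1)ρ)/j − r²], with r = 0 when own baseline is left out.
- Without own baseline: 1.000, 1.538, 1.875 and 2.105 for j = 1 to 4. Weighted: .075 × 4.413 + .70 × 2.105 = 1.805 per person; × 84 = 151.6 per arm. SE = √(2/151.6) = 0.115.
- With own baseline, r = .30: 1.099, 1.786, 2.256 and 2.597. Weighted: .075 × 5.140 + .70 × 2.597 = 2.204 per person; × 84 = 185.1 per arm. SE = √(2/185.1) = 0.104.
- Variance reduction: 1 − 151.6/185.1 = 18.1%.
- Effect detectable with 80% power, (1.96 + 0.84) × SE: 0.322 falls to 0.291 SD.

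**Range over the unknown correlation.**

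| ρ | r | SE without | SE with | Detectable effect (SD) |
|---|---|---|---|---|
| .30 | .10 | 0.115 | 0.114 | 0.322 to 0.319 |
| .30 | .30 | 0.115 | 0.104 | 0.322 to 0.291 |
| .30 | .50 | 0.115 | 0.081 | 0.322 to 0.226 |
| .50 | .50 | 0.130 | 0.102 | 0.364 to 0.285 |

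**Effect on power.** At the planned .58, power for the effect common to all visits is already 99.9% without own-baseline adjustment. The adjustment would matter if the true effect were smaller. At 0.30 SD, with ρ = r = .30, power rises from 74% to 82% (75% to 82% in a simulation of 1,000 trials).

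**The case against.** The strongest reply is that this is an efficiency suggestion about a plan that already works. The article is condensed, it says that the listed covariates will be included without saying that nothing else will be, and its power claim stands. The size of the gain also depends on a correlation that the article does not give. That correlation may be below .30: the TLFB records days in controlled environments, and many participants are in residential care of 30 to 90 days, so use in the 90 days before baseline may predict later use weakly. All of this stands, and it limits the point. It does not remove it, because the article states its covariate set and baseline use is not in it.

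A reader might also infer more than the article supports:

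- *That no outcome is adjusted for its own baseline.* CAPS-5 is.
- *That baseline TLFB is unused everywhere.* It may enter the imputation, whose predictors are not listed. That would not, however, adjust the analysis model for participants with observed outcomes.
- *That the TLFB comparison is biased, or its type I error inflated.* Under randomisation neither follows. With 84 per arm, a 1-in-20 baseline imbalance is 1.96 × √(2/84) = .30 SD, and at r = .30 it would shift the estimate by .30 × .30 = .09 SD. The unadjusted standard error already allows for that variation, so it is the same loss of precision seen from another side and not a second harm.
- *That describing the outcomes as changes (section 2.3) contradicts the model.* Randomisation makes the expected baseline difference zero, so on a linear scale the contrast at follow-up and the contrast in change have the same expectation.
- *That the main effect is diluted because baseline is one of the time points.* Section 2.8.2 speaks of follow-up time and makes baseline PTSD severity a covariate. Nothing in it puts baseline in the outcome vector.

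**Conclusion.** The point holds as a matter of precision. As listed, the model for one of the two primary outcomes lacks its own baseline, and so do the models for SIP-R, PHQ-9, BIPF, WHODAS and craving. For TLFB the avoidable variance in the visit-averaged contrast is about 18% with the planned dropout and 19% with complete data, if r = .30. It is about 2% at r = .10, and 39% to 51% at r = .50, depending on whether ρ is .50 or .30. These figures assume a linear scale, whereas the article leaves the form of the generalised linear mixed model open, so they are a guide to size only. The planned test is valid and the stated power is met. The change is worth making because it is nearly free and concerns a primary outcome.

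**What to change.** In section 2.8.2, or in the analysis plan if it has the same list:

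- Add baseline TLFB percent days of use as a fixed effect in the TLFB model.
- Add each other outcome's own baseline value to its model, where one is collected.
- Keep baseline PTSD severity in all models as planned.
- Put the same baseline variables in the imputation models, so that imputation and analysis agree.

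Make the change before any unblinded analysis, so that it cannot be read as a post-hoc choice. If the full plan already adjusts for own baselines, only the article's wording needs correcting.

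The cost is wording and one degree of freedom per model, with no new data. There is one side effect: if TLFB is modelled with a non-linear link, the treatment effect becomes conditional on baseline use, and the report should say so.
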